**Methods:**

This longitudinal observational study will recruit kidney transplant recipients aged ≤18 years who have received a parental donor kidney transplant across 4 countries (Australia, New Zealand, United Kingdom and the Netherlands) between 1990 and 2020. High resolution human leukocyte antigen (HLA) typing of both recipients and corresponding parental donors will be undertaken, to provide an in-depth assessment of immunological compatibility. The primary outcome is a composite of de novo donor-specific anti-HLA antibody (DSA), biopsy-proven acute rejection or allograft loss up to 60-months post-transplantation. Secondary outcomes are de novo DSA, biopsy-proven acute rejection, acute or chronic antibody mediated rejection or Chronic Allograft Damage Index (CADI) score of > 1 on allograft biopsy post-transplant, allograft function, proteinuria and allograft loss. Using principal component analysis and Cox proportional hazards regression modelling, we will determine the associations between defined sets of immunological and clinical parameters that may identify risk stratification for the primary and secondary outcome measures among young people accepting a parental donor kidney for transplantation. This study design will allow us to specifically investigate the relative importance of accepting a maternal compared to paternal donor, for families deciding on the best option for donation.

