The over-arching objective of this study is to address the current knowledge gap of the “NIMA paradox” by identifying potential differences in immunological compatibility between maternal and paternal donor kidneys and how this compatibility affects allograft outcomes. The study aims include:(i)Detailed immunological profiling for pediatric and adolescent recipients of parental donor kidneys with and without adverse allograft outcomes of the development of de novo donor-specific anti-HLA antibody (DSA), any acute rejection or allograft loss;(ii)Determine the association between different immunological risk profiles and adverse allograft outcomes; and(iii)Determine whether the associations between the immunological risk profiles and adverse allograft outcomes are modified by parental status and other clinical factors.

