### Clinical and laboratory parameters

In addition to the immunological profiling and outcome measures, a number of donor and recipient characteristics will be extracted from registries, databases and local hospital healthcare records where appropriate and available. Data to be extracted include donor factors of age, sex, body mass index, donor relationship to recipient, comorbid conditions and race; recipient factors of age, sex, body mass index, race, socio-economic status (SES; derived from post-code in Australia or alternative SES parameters in other countries), prior episodes of non-adherence to immunosuppressive agents or missed appointments (as recorded in healthcare records), comorbid conditions (including complex syndrome, urological, liver or cardiac diseases) and dialysis duration; and transplant-related factors of transplant era, ischaemic time, sensitization status of percentage class I and II panel reactive antibody (%PRA), types and intra-patient variability of the calcineurin-inhibitor levels; all of which are known to be associated with the clinical outcomes of interest. Information relating to measures of potential sensitization to maternal antigens, including complications in maternal pregnancy including infections, breast-feeding and prior pregnancies will be sought from respective donors (where available).

Specific outcome measures include acute rejection (and Banff classification) at any time point post-transplant (types, severity and response to treatment), allograft function (creatinine and eGFR at 3 and 6 months, then annually post-transplant), allograft failure (including causes of allograft failure) and death (including causes of death) will be extracted from ANZDATA registry or relevant sources in other countries; and kidney biopsy reports, rejection-related treatment and response to treatment, intensity of immunosuppression (therapeutic drug levels for calcineurin inhibitor [CNI] at 3, 6, 12, 24, 36, 48, and 60 months post-transplant), proteinuria (urine protein/creatinine ratios at 3, 6, 12, 24, 36, 48, and 60 months post-transplant if available) and number/duration of all-cause and cause-specific hospitalisations will be extracted from local hospital and laboratory data. The data will be entered into a password-protected database (unique to each site) at least up to 5-years post-transplant (or until allograft loss up to 10-years post-transplantation using linkage data to ANZDATA and other country-specific registries).

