### Statistical analysis

Data will be presented as mean ± standard deviation (SD) or number (proportion) for continuous and categorical variables, respectively, with means and proportion compared using *t-test* and the chi-squared test where appropriate. We will develop models with different numbers of archetypes and choose which to use as the final model according to the residual sum of squares using the “elbow” method [47]. The archetypal models will assign scores based on a combination of pre-transplant immunological and clinical (donor, recipient and transplant) parameters to each recipient using the time from transplant to the composite primary outcomes of de novo DSA, any episodes of acute rejection and allograft loss; with the scores totalling 1. Each parameter will be assigned to a single archetype cluster on the basis of the highest archetype score (corresponding to “high immunogenic risk” profile, comprising of immunological risk factors). Additional models accounting for pre- and post-transplant factors (such as donor age, non-adherence) will also be constructed. A principal component analysis will be constructed to visualize the data matrix used as the input for the archetypal analysis. The principal component analyses will produce two main results: (i) a correlation circle, and (ii) a projection of the individuals. The correlation circle allows for a graphical examination of the relationships among the pre-transplant immunological and clinical parameters and the graphical parameter contribution of the axes (positive or negative contribution: vector direction; strength of the contribution: vector length when projected on the axis). We will identify distinct groups (i.e. archetypes), each comprising of a well-defined set of immunological and clinical parameters that may improve the risk stratification for “adverse immunological outcomes” for those accepting a parental donor kidney for transplantation, and separately for those who have received maternal or paternal donor kidneys. The Australian and New Zealand cohorts will be the derivation cohort for these archetypes, which will be validated in the cohorts from the United Kingdom and the Netherlands. We will next seek to build a predictive model (combined cohorts) to examine the associations between the archetype clusters and other pre-specified covariates and the primary outcome using univariate Cox proportional hazards regression models. A multivariable Cox model will be constructed by selecting covariates by Group Lasso and Doubly Robust Estimation (GLiDeR), a method of variable selection to identify confounders using an adaptive group lasso approach that simultaneously performs coefficient selection, regularisation, and estimation across the treatment and outcome models. Bootstrap resampling with replacement or subsampling without replacement will be used to investigate and quantify model stability. Separate models will be constructed for each of the secondary outcomes. The results of the model and covariates will be reviewed to ensure clinical relevance. Deviance and score residuals will be plotted to evaluate for poorly predicted individuals or individuals that may have had large influences on model parameters. The performance of the integrated prognostic model will be assessed by computing a non–time-specific area under the curve (AUC) using the measure of concordance from Somer’s Dxy statistic. For assessment of model calibration, patients will be risk-stratified on the basis of their predictive index, which is the linear combination of the product of the multivariate model β coefficients and their individual covariate values. Kaplan-Meier survival curves will then be plotted for patients who are stratified into quintiles of their predictive indices. The validation cohort’s AUC will be determined and predicted and observed mortalities will be compared. The association between archetypes and adverse outcomes will be examined in the prospective cohort, and to examine how the addition of other newly developed novel immunological assays will improve the test performance of the models.

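### The analysis section describes no confounder-adjusted estimate, free of compatibility scores, of the maternal versus paternal difference on which the study is sized

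*Protocol article*

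**What the plan says.** **The contrast.** The Abstract (Methods) says the design will address the "relative importance of accepting a maternal compared to paternal donor, for families deciding on the best option for donation". The Discussion repeats that the findings should settle whether outcomes differ by donor parent and should inform families. The Sample size calculation section is built on the same contrast: 479 pairs, 1:1 maternal to paternal, 80% power, two-sided 5%, difference 0.10.

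**The pathway.** The Background gives the objective as "identifying potential differences in immunological compatibility between maternal and paternal donor kidneys and how this compatibility affects allograft outcomes". Aim (iii) is to "Determine whether the associations between the immunological risk profiles and adverse allograft outcomes are modified by parental status and other clinical factors".

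**The model.** Under Statistical analysis, the archetypal models "assign scores based on a combination of pre-transplant immunological and clinical (donor, recipient and transplant) parameters to each recipient". The next step is a predictive model "to examine the associations between the archetype clusters and other pre-specified covariates and the primary outcome using univariate Cox proportional hazards regression models". Then: "A multivariable Cox model will be constructed by selecting covariates by Group Lasso and Doubly Robust Estimation (GLiDeR". GLiDeR is described as a way to identify confounders that "simultaneously performs coefficient selection, regularisation, and estimation across the treatment and outcome models". The section does not say what the treatment is. Donor parent is recorded, among "donor factors of age, sex, body mass index, donor relationship to recipient, comorbid conditions and race" (Clinical and laboratory parameters), and archetypes are also to be derived separately for maternal and paternal recipients.

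**The concern.** Which parent donates determines the donor HLA, and therefore the eplet, amino-acid, electrostatic and T-cell scores. Under the study's stated objective these scores can be consequences of the choice of parent that in turn affect outcome. A family choosing between two willing parents needs the total difference, by whatever route it arises. A coefficient that holds the scores fixed answers another question: how much difference remains between a mother and a father of equal measured compatibility.

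A selector that looks for variables related to both exposure and outcome may also keep such scores and label them confounders. If no separate model leaves them out, the study could report a small adjusted difference that readers take as the answer to the family's question. It would also have no adjusted baseline against which to judge how far compatibility accounts for any difference.

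**Working it through.** **1. The powered contrast is maternal versus paternal.** Inputs from the Sample size calculation section: difference d = 0.10, 40% event proportion, 4 observations, correlation 0.5, 80% power, two-sided 5%. The second proportion is not given; 30% is assumed here.

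- Per arm, one observation: (1.96 + 0.8416)² × (0.40×0.60 + 0.30×0.70) / 0.10² = 7.849 × 0.45 / 0.01 = 353.2.
- Factor for 4 correlated observations: (1 + 3×0.5)/4 = 0.625, so n = 220.7 per arm, 441.5 in total.
- Continuity correction, n/4 × [1 + √(1 + 4/(nd))]²: 240.3 per arm, 481 in total.

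This is close to the stated 479. Adding the 10% missingness as well gives 500 to 534, depending on how it is applied, so not every stated input is reproduced together at 40% versus 30%. That is context only; the present point does not depend on it. What matters is that the two groups compared are maternal and paternal recipients.

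**2. What the described model would estimate.** The text allows three readings.

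| Role of donor parent | What is obtained for maternal versus paternal |
|---|---|
| GLiDeR treatment | Estimate conditional on whatever is selected; archetypes or scores may be kept as confounders |
| One covariate among others | Estimate conditional on the archetypes, which contain the scores |
| Not in the model | No adjusted estimate; at most a chi-squared or univariate Cox comparison |

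Under the first two readings the estimate would be free of the scores only if selection happened to drop them, not by design. Under the third, the comparison is unadjusted, in observational data from 1990 to 2020 in four countries, although the protocol itself lists many factors associated with outcome. The additional models mentioned for pre- and post-transplant factors are not described as leaving the scores out. Deriving archetypes separately by donor parent, and testing modification under aim (iii), do not estimate the overall difference.

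**3. How much could be lost.** This is an illustration; none of its drivers is in the protocol. Assume 40% versus 30% at 60 months under proportional hazards: HR = ln(0.60)/ln(0.70) = 0.5108/0.3567 = 1.43. If a share m of the log HR runs through the scores, the coefficient with the scores in the model is about 1.43^(1−m). A simulation (40,000 recipients per scenario, assumed score effect of 0.4 on the log-hazard scale per SD) gives:

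| Assumed m | 1.43^(1−m) | Simulated HR, score left out | Simulated HR, score included |
|---|---|---|---|
| 0% | 1.43 | 1.41 | 1.44 |
| 25% | 1.31 | 1.44 | 1.33 |
| 50% | 1.20 | 1.42 | 1.20 |
| 75% | 1.09 | 1.42 | 1.09 |
| 100% | 1.00 | 1.45 | 1.03 |

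The model without the score recovers the total effect throughout. The model with it ranges from no loss to near-complete loss.

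**The case against.** The strongest reply is that the model is meant for prediction. The protocol calls it predictive and prognostic and judges it by concordance, risk quintiles and a validation cohort. Variables on a causal path are no error in such a model, and none of the three listed aims is a total-effect estimate. This stands as a defence of the model for that purpose. It does not supply an estimate of the contrast used for the sample size and promised to families.

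A reader might infer that donor parent is in the multivariable model and that its effect will therefore be adjusted away. The documents do not support that. Donor parent is not named as a term; its presence is an inference from the list of extracted donor factors and from the mention of a treatment model. Nor is mediation the only mechanism proposed. The Background discusses tolerance after exposure to maternal antigens, under which the same mismatch could have different consequences by parent. That is effect modification, and it need not pass through the scores. A score-free but unadjusted comparison may also exist, if donor parent is among the pre-specified covariates taken into univariate Cox models.

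Finally, the covariate list and the identity of the GLiDeR treatment are details that a fuller plan could hold. That is fair for the list. But the article does fix the modelling strategy, down to a named selection method, and as written that strategy does not target the contrast for which the study was sized.

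**Conclusion.** The point holds in a limited form. The protocol sizes the study on a maternal versus paternal difference, yet no reading of the stated analysis provides, by design, a confounder-adjusted estimate of that difference that leaves out the compatibility scores. It should be corrected; it does not invalidate the planned prognostic model.

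The possible attenuation is unknown. It is nil if the effect does not run through the measured scores. The illustrative fall from 1.43 to 1.20 rests on an assumed 30% comparator, proportional hazards and an assumed mediated share of one half. It shows what could happen, not what will. The stronger statement, that a real difference would be reported as little or none, is not supported.

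**What to change.** Name donor parent as the exposure for the maternal versus paternal question and pre-specify two Cox models for the primary outcome:

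- **Total-effect model:** donor parent plus pre-transplant confounders already collected, for example recipient age, sex and race, donor age, transplant era, country and dialysis duration. Exclude compatibility scores, archetypes and post-transplant variables. This is the estimate for families and the one that matches the sample size contrast.
- **Second model:** the same terms plus the compatibility scores and a donor-parent-by-score interaction, which serves aim (iii).

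Report the two side by side. Describe the change in the donor-parent coefficient without presenting it as a formal mediated share, because that reading assumes no interaction between parent and score, and aim (iii) asks about exactly such an interaction. Keep the archetype and GLiDeR model as the prognostic model, and state what its treatment variable is.

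The cost is a few sentences of analysis text and one or two extra models. No new data are needed, and nothing planned is lost.

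### Covariates for a model presented and judged as prognostic are chosen by a confounder-selection method that needs a treatment model, and no treatment is named

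*Protocol article*

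**What the plan says.** All the modelling text is in the Statistical analysis section of the protocol article. The Cox modelling is introduced this way: "We will next seek to build a predictive model (combined cohorts) to examine the associations between the archetype clusters and other pre-specified covariates", with the primary composite outcome as the endpoint. Covariates of the multivariable Cox model are then to be selected by GLiDeR. The article explains that this is "a method of variable selection to identify confounders using an adaptive group lasso approach" and that it "simultaneously performs coefficient selection, regularisation, and estimation across the treatment and outcome models".

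The evaluation that follows is that of a prediction model: "The performance of the integrated prognostic model will be assessed" by a concordance-based AUC. Patients are then grouped into quintiles of a predictive index for calibration, and an AUC is computed in the validation cohort.

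Two variables could be the treatment, and the section assigns that role to neither:

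- **Donor parent.** The abstract says the design will "specifically investigate the relative importance of accepting a maternal compared to paternal donor", and the Sample size calculation section compares maternal with paternal donors 1:1. Aim (iii) in the Background, however, treats parental status as a modifier of the association between immunological profile and outcome.
- **Archetype cluster.** This is the main predictor in the sentence that introduces the Cox model. The archetypes are built from immunological, donor, recipient and transplant parameters.

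The Clinical and laboratory parameters section lists the data to be extracted, including "donor factors of age, sex, body mass index, donor relationship to recipient". It does not say which of these variables are offered to GLiDeR.

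**The concern.** A confounder exists only in relation to an exposure. A method that looks for confounders through a treatment model and an outcome model together is built to serve an exposure-effect estimate. Selection for prediction asks a different question: which variables improve discrimination and calibration for the outcome. The two can disagree, because a variable's relation to the treatment carries weight in the first task and none in the second.

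With no treatment named, two analysts could follow the text faithfully, one taking donor parent and the other archetype cluster, and arrive at different covariate sets. The AUC, predictive index and quintile curves would then describe a model whose covariates were not chosen for prediction. The same model would not give a clearly defined adjusted effect either. This matters because the article says its findings should inform the choice between parental donors, which makes it important to know whether a reported coefficient is a prognostic weight or an adjusted contrast.

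**Working it through.** The plan states no figure on this point, so there is none to reproduce. The check has two parts.

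**1. Method against use, from the text**

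| Item | What the Statistical analysis section fixes |
|---|---|
| Purpose of the selection method | Finding confounders |
| Models the method works across | Treatment and outcome |
| Treatment variable | Not named |
| Purpose of the Cox model | Prediction, together with associations of archetype clusters and covariates with the outcome |
| Criteria for judging the model | Concordance AUC, predictive index, quintile curves, validation AUC |

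Every performance criterion concerns prediction, while the selection criterion concerns confounding. The mismatch lies between two things the article itself states.

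**2. What each candidate treatment would imply**

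*Donor parent.* Every donor is a mother or a father, so donor sex reproduces the exposure exactly, and donor relationship records it. An illustration shows the consequence if donor sex is offered as a candidate.

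- Inputs from the article: 520 expected pairs and 1:1 allocation, giving 260 maternal and 260 paternal.
- Assumed inputs: donor age normal with mean 40 and SD 7, mothers shifted 2 years younger; donor BMI normal with mean 26 and SD 4.
- Treatment model: logit P(maternal) = b0 + b1·age + b2·BMI, then the same with b3·(donor female) added.

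| Treatment model | Fitted P(maternal) |
|---|---|
| Without donor sex | about 0.14 to 0.80 over all pairs |
| With donor sex, unpenalised | lowest among mothers about 1.000; highest among fathers about 7e-14 |
| With donor sex, L1 penalty 1.0 | lowest among mothers 0.979; highest among fathers 0.015 |
| With donor sex, L1 penalty 0.001 | lowest among mothers 0.9999; highest among fathers 0.00006 |

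An outcome design holding donor parent, donor sex and donor age has rank 2 of 3, so the effects of parent and donor sex cannot be told apart.

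The penalised case can fail without warning. At penalty 1.0 the inverse-probability weights would be at most 1/0.979 = 1.021 for mothers and 1/(1 − 0.015) = 1.015 for fathers. All weights are close to 1, so weighting would adjust for almost nothing. Without donor sex the two groups overlap and the problem disappears.

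These are ordinary and L1-penalised logistic fits, not runs of GLiDeR. They show the separation, not the behaviour of the full procedure.

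*Archetype cluster.* Clusters are derived from donor, recipient and transplant parameters. If some of these parameters were also offered as candidate confounders, they would partly determine cluster membership, and overlap could again be poor. The article does not say whether the candidates overlap the cluster inputs, and no calculation was made for this case.

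**The case against.** The strongest reply is that the model has a mixed purpose. Aims (ii) and (iii) are about association, and the introductory sentence speaks of examining associations with archetype clusters. Adjusting an association for confounders and also reporting the model's discrimination is not self-contradictory. The text also points to archetype cluster as the likely exposure, and it adds resampling checks of stability and a clinical review of the covariates. Naming the exposure and listing candidates is detail that an article may leave to the full protocol or SAP.

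Part of this stands. The candidate list may well sit elsewhere, and its absence is not held against the article. Archetype cluster is a reasonable guess at the exposure. The objection does not remove the mismatch, because the article itself chose the method, stated its purpose and attached it to a model that it assesses only as a prognostic tool. A later candidate list would still leave confounder selection feeding a prediction model.

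A reader might infer something stronger: that donor sex makes the planned analysis degenerate, or that the doubly robust estimate is undefined. The documents do not support this. The list holding donor sex and donor relationship is a data-extraction list, and in a cohort made up only of parental donors the relationship field is simply how the exposure gets recorded. Nothing says that either variable is a candidate, or that donor parent is the treatment. Under a penalised method the fitted probabilities also come close to 0 and 1 without reaching them.

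**Conclusion.** The concern holds as a mismatch between method and use. A selection method described as finding confounders, and needing a treatment model, chooses the covariates of a model judged on prediction, with no treatment named. This conclusion rests only on the article's own description of the method and the model.

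The loss in predictive accuracy cannot be sized from the document. Near-complete separation (0.979 against 0.015 at an L1 penalty of 1.0) applies only if donor parent is the treatment and donor sex or relationship is offered; the figures also rest on the assumed age and BMI distributions. The overlap problem with archetype cluster as treatment is conditional in the same way and was not quantified. The mismatch should be corrected before analysis, but it does not make the study unworkable.

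**What to change.** Separate the two tasks in the Statistical analysis section.

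1. **Prognostic model.** Select covariates by penalised Cox regression (group lasso or elastic net) on the time-to-event outcome alone, tuned by cross-validation, with the archetype scores and donor parent kept in the model. Report the AUC, predictive index and calibration from this model.
2. **Exposure-effect analysis.** Use GLiDeR only here. Name the exposure and restrict candidates to pre-transplant variables. For the maternal versus paternal contrast, exclude donor sex and donor relationship from the candidates. If archetype cluster is the exposure, state whether any cluster inputs are also candidates, and check overlap.

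The cost is revised wording, one extra model fit and two covariate sets to report instead of one. No new data are needed.

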### Outcome measures

The primary outcome is the composite of de novo DSA (defined as mean fluorescence intensity [MFI] of over 500), or any biopsy-proven acute rejection or allograft loss (defined as returning to dialysis or death with functioning allograft) after parental donor kidney transplantation up to 60-months post-transplant. Secondary outcomes are individual components of the primary composite outcome (development of de novo DSA, any biopsy-proven acute rejection, allograft loss at 60-months post-transplant but also extended follow-up to 120-months post-transplant), acute or chronic AMR (including the presence of TG) or Chronic Allograft Damage Index (CADI) score of > 1 on allograft biopsy post-transplant, allograft function (creatinine-derived estimated glomerular filtration rate [eGFR] using the Chronic Kidney Disease-Epidemiology Collaboration [CKD-EPI] equation for recipients aged ≥16 years [32] or bedside Schwartz equation for recipients aged < 16 years [33–35]), and urine proteinuria.

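### The step labelled calibration plots observed survival by quintile of the predictive index, so it shows discrimination and cannot detect a wrong calibration slope or baseline risk for the primary composite

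*Protocol article*

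**What the plan says.** All of the relevant text is in the protocol article, mostly under Statistical analysis.

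- **Calibration.** "For assessment of model calibration, patients will be risk-stratified on the basis of their predictive index". The index is defined as a quantity "which is the linear combination of the product of the multivariate model β coefficients and their individual covariate values". The display is: "Kaplan-Meier survival curves will then be plotted for patients who are stratified into quintiles of their predictive indices". The text does not say that model-predicted curves are added.
- **Discrimination.** Performance is summarised by a non-time-specific "area under the curve (AUC) using the measure of concordance from Somer’s Dxy statistic".
- **Validation.** The archetypes are derived in Australia and New Zealand, "which will be validated in the cohorts from the United Kingdom and the Netherlands". For the validation cohort the AUC is to be determined and "predicted and observed mortalities will be compared".
- **Data for the model.** "We will next seek to build a predictive model (combined cohorts").
- **Outcome.** Under Outcome measures the primary outcome is de novo DSA, biopsy-proven acute rejection or allograft loss to 60 months. Death enters only within "allograft loss (defined as returning to dialysis or death with functioning allograft").

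**The concern.** Calibration is agreement between the risk a model predicts and the risk that is observed. The procedure given that name has two inputs: the order of patients on a Cox linear predictor, and their observed event times. A linear predictor contains no baseline hazard and is not an absolute risk, and predicted event probability does not enter the display. The plot therefore answers a question about separation of risk groups, which the concordance measure already addresses.

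The Discussion says the findings can inform families of potential risks and expected long-term outcome after a maternal or paternal kidney. That use needs absolute risks that are about right. A model fed with many related mismatch scores may predict too extremely in new patients, and baseline risk may differ between countries. Both are errors of slope or level. If well-separated curves are reported as evidence of calibration, readers could trust predicted risks that have not been tested against the composite.

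**Working it through.** The plan gives no figure for this step, so there is none to reproduce. The check has an algebraic part and an illustration.

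**1. Invariance.** Write the index as LP = Σβx and the predicted 60-month risk as 1 − exp(−H·exp(LP)), where H is the baseline cumulative hazard at 60 months. Replace LP by k·LP with k > 0, or H by c·H with c > 0. The order of patients is unchanged, so the quintiles are unchanged. The observed times in each quintile are then the same, and so are the Kaplan-Meier curves. Concordance depends only on the order as well. The predicted risk does change.

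**2. Simulation with 40% risk.** The 60-month risk of 40% and the 520 pairs come from Sample size calculation. The other inputs are assumptions: LP normal with SD 0.8, exponential event times and random censoring. Four models with distorted slope or baseline were compared with the perfect model. At n = 520 and at n = 20,000, quintile membership was identical in every model and the largest difference in Kaplan-Meier 60-month risk was 0.000. Concordance was 0.6896 for all five models (computed at n = 520). At n = 20,000, 60-month risk by quintile was:

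| | Q1 | Q2 | Q3 | Q4 | Q5 |
|---|---|---|---|---|---|
| Observed (all models) | 0.149 | 0.250 | 0.362 | 0.504 | 0.734 |
| Predicted, perfect | 0.145 | 0.257 | 0.364 | 0.499 | 0.735 |
| Predicted, slope ×2 | 0.058 | 0.179 | 0.366 | 0.648 | 0.946 |
| Predicted, slope ×0.5 | 0.232 | 0.307 | 0.365 | 0.429 | 0.547 |
| Predicted, baseline ×2.5 | 0.321 | 0.523 | 0.676 | 0.820 | 0.953 |
| Predicted, baseline ×0.4 and slope ×2 | 0.024 | 0.076 | 0.168 | 0.348 | 0.755 |

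The plan's display contains only the first row. The difference between models appears once a predicted row is set beside it.

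**3. Slope error alone, mean risk matched.** Here LP has SD 0.6, true risk is 1 − exp(−0.5·exp(LP)), and H is re-solved so that mean predicted risk equals mean observed risk. Observed risk by quintile is about 20, 31, 39, 49 and 68%, with mean (20+31+39+49+68)/5 = 41.4%. With coefficients twice too large (calibration slope 1/2 = 0.5), predicted risk is about 9, 21, 36, 57 and 86%. The top quintile is 86 − 68 = 18 points too high and the bottom 20 − 9 = 11 points too low. With coefficients 1.5 times too large, predicted risk is about 13, 25, 37, 53 and 78%, so the top quintile is 78 − 68 = 10 points too high.

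**4. Does another stated step fill the gap?** The predicted-versus-observed comparison names mortality. The Cox model is for the composite, in which death is one part of one component, so agreement on mortality would not establish agreement on the composite. The model is also built on the combined cohorts, which include the United Kingdom and Dutch recipients used for validation. A comparison in those recipients is therefore partly a check on the fitting data.

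**The case against.** A reader might infer that predicted risk is never used anywhere in the plan. The document does not support that. It plans a comparison of predicted and observed mortalities, and it plans deviance residuals, which are built from the model's predicted cumulative hazard and so respond to rescaled coefficients. What remains is narrower: the first names an outcome other than the composite, and the second looks for poorly predicted individuals in the fitted data and is not offered as calibration.

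A reader might also infer that any badly miscalibrated model would give the same curves as a perfect one. That holds only when the ordering is preserved. Real overfitting adds noise to coefficients, misranks new patients and narrows the separation of the curves. An unpenalised Cox fit has slope 1 in its own data, and the planned lasso penalty shrinks coefficients, so a doubled slope would not be expected there. The 18-point figure is therefore no forecast. The plan also sets no pass rule for the quintile plot, so it cannot be said that a poor model would formally pass.

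The study aims concern profiling, association and effect modification, and individualised risk assessment is listed only as a potential use. This limits the importance of the point, although the Discussion does speak of informing families about risk.

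Finally, an article may leave an overlay of predicted curves to a fuller document. That is fair for missing detail. Here, however, the article names a specific procedure as the calibration assessment, and that procedure as described does not measure calibration.

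**Conclusion.** The point holds in a limited form. As written, the calibration step displays discrimination and cannot detect a wrong slope or a wrong baseline risk. This follows from the algebra and needs no simulation assumptions. No stated step sets predicted beside observed risk for the primary composite, and the one comparison of that kind uses mortality in a cohort that also contributes to fitting the model.

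The size of any miscalibration is unknown. The errors of 18 and 11 points rest on an assumed slope of 0.5 and an assumed index SD of 0.6; the ranges in the table rest on an SD of 0.8 and chosen distortions. The point affects how far predicted risks can be trusted. It does not affect the estimated associations between archetypes and outcome. The wording should be changed before the model is evaluated.

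**What to change.** Under Statistical analysis, for the primary composite:

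- Overlay the mean model-predicted event-free curve on the observed Kaplan-Meier curve in each quintile of the predictive index.
- Report the calibration slope and the observed/expected ratio at 60 months, each with a 95% CI.
- Compute these in data not used to fit the model, or correct them for optimism with the bootstrap resampling already planned for model stability.
- Replace mortality by the composite in the predicted-versus-observed comparison.
- Keep the plain quintile plot and describe it as a display of discrimination.

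This costs a few sentences of text and a small amount of code, and it needs no new data. If out-of-sample figures are preferred, the model must be fitted without the validation countries, which leaves fewer events for fitting; optimism correction avoids that. Reported calibration may look less favourable.
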